### Data analysis

Data will be analysed using a range of conventional statistical methods used in bio-statistics as well as model based methods more commonly found in the scientific statistical literature.

The independent samples t-test is commonly used when two separate sets of independent, randomly selected and normally distributed samples are available, one from each of the two populations being compared. However as explained previously, our project design makes random selection of Test and Control patients impossible and the alternative Before and After Control Intervention (BACI) design was adopted [22]. This design involved the site PO selecting the test patient first and then selecting from the remaining eligible test patients the controls that best match each test patient in turn.

As a consequence statistical comparisons in this study can only be validly made on Test – Control matched pairs and tested using the paired samples or repeated measures t-tests. We expect to obtain data from 125 test patients and up to 250 control patients. When two or more matched Control patients are available their data is averaged.

Data will be routinely tested for normality and if not normal, the appropriate transform, often log functions, will be applied to normalise the data prior to applying paired samples or repeated measures t-tests. Baseline characteristics will be described for time intervals as mean ± SDs for continuous symmetrical variables and means and 95% Confidence Intervals (CI) for skewed data. When before intervention data are available on outcomes, then the differences between the test and their controls will be tested to examine if there are any differences in the before intervention period. This process will be examined visually by examining boxplots of the time stamped differences (e.g., differences between the respective monthly variables eg. hospital costs) between test and control patient outcome measures.

As is common in the life sciences our data may be lognormal when not zero and may contain numerous zero values. In these circumstances the data will be modelled using a lognormal distribution for positive values, together with an additional probability mass at zero. This type of distribution is commonly referred to as delta-lognormal. 95% Confidence limits are calculated according to the method of Zou, Taleban and Huo [37].

All statistical tests for the before intervention period will be two-sided but all tests of whether the intervention made a difference will involve a one-tailed matched pair t-test, and either a p value of 0.05 or less will be used to indicate statistical significance or a confidence interval will be provided to judge the impact of the intervention. Statistical analysis will be performed using Stata Release V.12 (TX: StataCorp LP), SPSS 17, R package [38] and Microsoft Excel.

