Following the signing of a consent form and completion of the Entry Questionnaire, Test patients are connected to the internet and supplied with the TMC Telemonitoring system and trained on its use by the Project Officer (PO) at each site. Their vital signs and questionnaire responses are subsequently monitored on a daily basis by the Clinical Care Coordinator (CCC). On site visits and technical support as well as the obtaining of Consent and the administration of Exit questionnaires are the responsibility of the PO.

Control patients also complete the Entry questionnaire but otherwise continue to receive normal care. For each intervention participant, as many as six control candidates are automatically case matched on gender, age, chronic condition and Socio-Economic Indexes for Areas (SEIFA) [24]. On their consent the two closest matching control candidates commence as participants in the study. The remaining four candidates are held in reserve. Table 2 below demonstrates the case matching process.

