**Table 2 Tab2:** **Example of case matching of Control patients with Test patients**

Test/control	Age	Gender	Major diagnosis	Seifa ^1^ index for postcode	Strength of match (perfect match = 0)
Test	54	M	COPD	1023	
Control	56	M	COPD	1025	1.68^2^
Control	54	F	HD	1022	2.16^3^
Weights	0.2	1	1	0.16	

^1^SEIFA 2011 Socio-Economic Indexes for Areas [24]. SEIFA provides measures of socio-economic conditions by geographic area.

^2^|54-56| × 0.2 + 1 × 0 + 1 × 0 + |1023-1015| × 0.16 = 1.68.

^3^|54-54| × 0.2 + 1 × 1 + 1 × 1 + |1023-1022| × 0.16 = 2.16.

Generally, the closer the match the greater the likelihood of finding a significant result with a smaller number of samples if the impact is relatively small.

Ideally, as many as four matches are sought for each Test patient, and the closest match is then selected as the case matched control for that Test patient. In many cases only one acceptable match may be available.

Following a change of Government in Australia, the requirement to connect patients to the high speed National Broadband Network was removed and as consequence, approximately half of our trial patients will be connected to a variety of NBN, ADSL, ADSL2 and VDSL network services with a minimum level of service of 2Mbps download and 1Mbps upload. Those on the NBN service were guaranteed a download speed of 25Mbit/sec and an upload speed of 5Mbit/sec.

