 Log of cost plus one will be treated as normally distributed with log of the number of days in the month as the offset. Sometimes the square root transformation may be used to stabilise the variance. We are hoping there are not too many zero cost periods or zero counts. If this fails we will use the zero adjusted inverse Gaussian distribution for the model – fitting them using the **gamlss** (package in R) using random() for including random effects [40]. τ_k(i)_ is a random effect in the above model that is assumed to be normally distributed with mean zero and constant variance. The assumption in the previous dot point and the assumption for e_ijk_ in the model thus assumes that measurements made at the same time segments (e.g., on the same quarter) have the same correlation and homogeneous variances for all repeated measures. The above model treats the study as a fully-designed experiment with the appropriate randomisation. However, this is seldom the case because most impact studies are observational in nature. The assumption is that each measurement for the intervention patients is matched with a measurement for one or more control patients. This blocking is expected to control for the non-randomisation in the design. The complexity of this analysis can be greatly reduced by taking the differences between the Test and Control measurements The model above tests whether a significant change has occurred by testing the significance of the interaction term of the model for the before after indicator variables and the control-intervention indictor variable. For example if the coefficient for intervention patients and after intervention duration has lower insured costs that before the intervention after adjusting for controls, then the intervention has had a significant impact on costs. The random effects terms and random error term are assumed to be uncorrelated in time. The control patient is generally selected to control for all covariates. In this study this means that control patients should be identical to the intervention patient in terms of age, gender, SEIFA index and major comorbidities. The samples are selected over time (therefore they are time series rather than repeated measures made at the same time). So it may seem unlikely that the model errors will be independently distributed but hospital costs are measured a month apart and this should be enough to for the assumption of independence to be valid. The assumption that all repeated measures have the same variance is unlikely to be true. If the gamlss package is used then this change in variance can be accounted for. Although theoretically longitudinal data structures can be modelled by random effects in gamlss [40] but at present no computationally feasible implementation for large sample sizes and complex models exists. Assume that the trend in the response variable over time is approximately linear. This assumption is likely to be reasonable over the 5 year study period, but is unlikely to be true for longer time periods.

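### Averaging two controls before a log or square-root transform shifts any Test-minus-Control level comparison towards lower use in test patients; the before-after interaction is largely protected

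*Protocol article*

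**What the plan says.** All references are to the protocol article.

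- **Averaging.** Data analysis: "When two or more matched Control patients are available their data is averaged". It does not say whether this is done on the raw or the transformed scale.
- **Transform.** The next paragraph of that section says that, where data are not normal, "the appropriate transform, often log functions, will be applied to normalise the data prior to applying paired samples or repeated measures t-tests". Classical BACI designs and extensions names the transforms: "Log of cost plus one will be treated as normally distributed" and "Sometimes the square root transformation may be used to stabilise the variance". Table 6 uses log(cost+1) for costs and the square root for counts.
- **Test.** Data analysis: "all tests of whether the intervention made a difference will involve a one-tailed matched pair t-test", and "a p value of 0.05 or less will be used to indicate statistical significance". It does not say whether the paired quantity is the after-period value or the before-after change.
- **Before-period check.** The same section tests Test-Control differences before the intervention, two-sided. This is a comparison of levels.
- **Effect in the model.** Classical BACI designs and extensions defines the effect as the movement of test patients from before to after relative to their controls, tested by the period-by-group interaction.
- **Number of controls.** Selection of trial participants says that "the two closest matching control candidates commence as participants in the study". The text under Table 2 says that "the closest match is then selected as the case matched control for that Test patient", and adds that many test patients may have only one acceptable match. The BACI section speaks of one or two.

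**The concern.** Averaging controls is harmless when it is done on the scale of analysis. It is not harmless when a concave transform follows. The transform of an average is at least as large as the average of the transforms, and test patients are never averaged. With identical populations and no effect, Test minus Control is then negative on average, which looks like reduced use of care.

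Two uses are exposed. The before-period check, meant to show that the groups started alike, can show a false gap. The one-tailed paired test, if run on after-period values, takes the whole error in its rejection tail. (The article does not state the tail; the Abstract expects less unscheduled hospitalisation, so the lower tail is assumed here.) Because the number of controls varies between sets, so does the offset.

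**Working it through.** **The plan's own figures.** Table 6 gives power for the paired test, for example 0.84 for log(MBS in hospital costs+1) with a shift of 1 and an effective sample size of 30. This cannot be reproduced, because the correlation and standard deviation appear only as symbols. Inverting the noncentral-t power with n = 30 and one-sided 0.05 gives an implied SD of the differences of 2.03; for the square root of admissions (shift 0.5, power 0.99) it is 0.67. Neither gives the spread or the share of zeros in individual patients, so these are assumed below.

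**Mechanism.** Let f be the transform, T the test patient and C1, C2 the controls, all from one distribution. Define b = E f((C1+C2)/2) − E f(C1), which is ≥ 0 for concave f. With no effect, E[f(T) − f((C1+C2)/2)] = −b.

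Illustrative values (not from the article):
- Monthly costs of 0 and 200: log(100+1) = 4.62, against (0 + log 201)/2 = 5.30/2 = 2.65. The gap is 1.96.
- Counts of 0 and 2: √1 = 1, against (0 + 1.41)/2 = 0.71. The gap is 0.29.

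**Size in a level comparison.** Simulation with no effect, 125 sets of one test patient and two controls, 4000 replicates, one-sided 0.05, averaging before the transform:

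| Assumed outcome | Mean offset | False reduction |
|---|---|---|
| log(cost+1), log-SD 0.5 | −0.05 | 24% |
| log-SD 1 | −0.17 | 52% |
| log-SD 1, match correlation 0.6 | −0.09 | 37% |
| log-SD 1.5 | −0.33 | 72% |
| log-SD 1, 30% zeros | −0.85 | 95% |
| log-SD 1, 70% zeros | −0.79 | 84% |
| √count, overdispersed, mean 0.2 a month | −0.06 | 35% |
| √count, mean 1 | −0.14 | 56% |
| √count, mean 3 | −0.13 | 41% |

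A separate run with independent patients, mean log 5 and log-SD 1 gave 58%, 95% and 83% for 0%, 30% and 70% zeros. If only half the sets have two controls, these fall to 21%, 42% and 37%. With 30 sets instead of 125, the false-reduction rates run from 12% to 47%. The two-sided before-period check rejects in 15-90% of trials at 125 sets.

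**Transforming each control first.** The offset is about 0 and the rejection rate is 4.5-6.3% in every setting.

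**Before-after contrast.** The expected change in the Test-Control difference is effect − (b_after − b_before). If b is the same in both periods it cancels: rejection is 4.4-5.8% even with averaging first. If the distribution shifts equally in both groups, the residual goes either way:

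| Common shift, before to after | One-sided rejection |
|---|---|
| zeros 80% to 60% | 19% |
| log-SD 1 to 1.2 | 12% |
| mean count 0.1 to 0.2 | 11% |
| zeros 40% to 30% | 2.8% |
| mean count 0.2 to 0.1 | 1.8% |

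If a share p of sets falls from two controls to one, b_after = (1 − p)b and the bias is +p·b, which is against finding a reduction. For p = 20% (assumed) this is 0.2 × 0.17 = 0.03 log units at log-SD 1 without zeros, and 0.2 × 0.85 = 0.17 with 30% zeros. For scale, a 20% reduction is −log 0.8 = 0.22, and Table 6 uses a shift of 1 for costs.

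**Variance.** On the transformed scale with independent patients, a set with two controls averaged after transforming has variance σ²(1 + 1/2) = 1.5σ², and a set with one control has 2σ². The model assumes homogeneous variance.

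**The case against.** The strongest reply is that the article never fixes the order. Averaging may be meant on the transformed scale, where there is no bias, and a condensed article can leave such detail to a fuller plan. That stands as a limit: the faulty order is the natural reading of two consecutive paragraphs, not a stated rule.

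A second reply is that the effect is defined as relative before-after movement, where a constant offset cancels. This also stands. A reader might infer that the trial's BACI result is biased towards a reduction. The documents do not support that: the interaction is close to nominal when outcome distributions and numbers of controls are stable, and otherwise the bias has no fixed sign.

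Third, the article has other routes for many zeros: a delta-lognormal distribution in Data analysis and a zero-adjusted inverse Gaussian model in the BACI section. The rates of 84-95% therefore apply only if log(cost+1) is used despite many zeros. Without zeros, 24-72% remains for costs.

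Fourth, the model indexes individual patients, and the Figure 5 caption refers to 125 Test and 250 Control patients, so the mixed model may already use each control's record. That would clear the model, but not the paired t-tests, for which the averaging sentence is written.

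**Conclusion.** The point holds in a conditional form. If raw control values are averaged and then transformed, the before-period level check, and the one-tailed paired test if applied to after-period values, are shifted towards lower use in test patients. The false-reduction rate is roughly 25-95% against a nominal 5% with 125 sets of two controls each. It is lower with correlation within sets or with single-control sets.

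The direction follows from concavity. The sizes rest on assumed log-SDs, zero shares, count means and correlations, since the article gives none. The before-after interaction is not systematically biased towards benefit. The disagreement over one or two controls matters here because it decides which sets carry the offset.

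**What to change.** 1. State that each control's value is transformed before controls are averaged, or analyse each control's own record in the mixed model with a matched-set random effect. The second option also handles sets with different numbers of controls.
2. State that the one-tailed paired test is on the before-after change in the Test-Control difference, and run the before-period check on the same corrected scale.
3. Reconcile Selection of trial participants, the text under Table 2, Data analysis, and Classical BACI designs and extensions on whether one or two controls per test patient are analysed.

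The cost is a few sentences and about one line of analysis code. No new data are needed.

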 Demonstrate and document how telehealth services can be successfully deployed across Australia, by piloting services in five different settings across five states with a range of health service provider’s, including Local Health Districts, Medicare Locals and not for profit community organisations. This will be demonstrated by deploying and demonstrating the operation of Telehealth monitoring in a multi-site multi-state case matched control trial (Before-After-Control-Impact (BACI) design) of chronically ill patients living in their own homes in the community. This has never previously been attempted in Australia. Provide the clinical and health economic evidence on how Telehealth services can be scaled up nationally to provide an alternative cost effective health service for the management of chronic disease in the community. Provide evidence that at home telemonitoring has the potential to reduce unscheduled admissions to Accident and Emergency (A&E) compared to the control group. Provide evidence for an impact on hospital admissions, mortality, clinical events and symptoms and improvements in functional measures and patients' and carers’ experiences with care. Evaluate health economic benefits Evaluate impact on clinical work force availability and deployment Evaluate impact of human factors (acceptability, usability by patients, carers, nurses, GPs and administrators, impact on workplace culture) Evaluate impact of workplace culture Evaluate impact of organisational change management and business processes Develop a new evidence based data analytical technique for the risk stratification of patients’ health status daily and demonstrate that this facilitates the management of large numbers of patients by orchestrating an optimal and timely allocation of resources to avoid unnecessary hospitalisation

For each of the above objectives, operation of the trial at five different sites representing a range of different models for the management of chronic disease in the community will allow the identification and analysis of site specific differences in workplace culture, organisational change management and staff and management capabilities that contribute to differences in measured health, social and economic outcomes.

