**Table 5 Tab5:** **Data Model for evaluating outcomes and objectives**

Objective/outcome	Data variable	Data source
Define the study cohort/confirmation of selection critera and exclusions	Admitted to hospital for their condition at least twice in the previous year, or ≥ 4 times in previous five years	Hospital health roundtable records - obtained from local hospital for previous five years.
		• Date admitted
	Exclusions are mental health and cancer patients	• Date discharged
		• Reason for admission (ICD 9/10 Codes)
		• Procedures carried out
Establish if telehealth	Number of unscheduled admissions to hospital for their condition	MBS Flag (In hospital) Health roundtable record
Improves patient outcomes/reduced hospitalisation		• Date admitted
		• Date discharged
		• Reason for admission (ICD 9/10 Classification)
		• Medication administered
		• Procedures carried out
Establish If telehealth improves patient outcomes/reduced use of clinical services (Impact on clinical workforce availability and deployment)	Number of visits to/by GP	MBS records
	Number of visits to/by specialists	MBS records
	Number of visits by community nurse	MBS records
	Number of visits to/by allied health (ie occupational therapist)	MBS records (If reimbursable from Medicare)
	Changes in prescription history	PBS
	Communication with CCC	CCC Logs from CSIRO Portal
Organisational change management and impact on workplace culture	Administrative/operational changes implemented/required in order to implement the Telehealth service.	Questionnaires and structured interviews.
		• Within first three months
		• Every six months thereafter
Useability of monitoring equipment	Compliance with monitoring schedule, recorded daily.	TMC Logs
	Extra measurements taken by patient (When? Which?)	TMC Logs
	Compliance with questionnaire administration (When? Which?)	TMC Logs
	Use of video conferencing	TMC Logs
	Overall data usage	iiNET provided logs
Useability/acceptability	Ease of use	Questionnaires delivered via TMC
For patients of monitoring Equipment	Quality of training received	• One month after first deployment
	Patient embarrassment if visitors know they are being monitored	• Midpoint of trial
	Acceptability as an item of furniture	• At end of trial
	Easy or hard to take measurement	
	Important/not important in patients' self management	
	Responsiveness of clinical care coordinator in responding to changes	
	Quality of training received	

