### Classical BACI designs and extensions

Because of the temporal nature of health data and the underlying trends caused by the increasing burden of chronic disease with increasing age, before and after comparisons can be difficult or inconclusive. In this study we will have available patient data for a period of 4.5 years including the period of the intervention which may vary from 6–18 months.

Since standard BACI design cannot be used when study variables trend over time, we adopt a mathematical approach using a mixed linear effects model (*lme*) to assess the intervention while trying to adjust for the time varying mean in simple ways. The *nlme* library in the statistical package R is used to perform the analysis according to the methods of Pinheiro et al. [39].

The Test patients will be matched with one or two controls and the relative movement of Test patients’ outcomes before and after the start of the intervention will be compared to that of their Control patients. The before-and-after comparisons use control patients to adjust for background variations in such variables as public health policy impacting on costs and even for example, climatic conditions during the before and after intervention period.

Let *y*_*ijk*_ be any of the variables to be analysed, such as for example, the PBS/MBS/Hospital costs value per unit time period (month) at time k during period *i* (before or after the intervention), for patient *j* (control or intervention patient). The model for the response value is given by

where:

 *μ* is the overall mean *α*_*i*_ is the effect of period (before and after) τ_k(i)_ is the repeated measures within periods (assumed to be a random effect) β_j_ is the effect on jth matched patients (intervention or control) (αβ)_ij_ is the interaction between period and matched patient groups θ is the overall slope relating to time in months if no differentiation is made between the groups (B-A, C-I) θ_ij_ is the slope relating to time (k) in months for the various combinations of the groups (B-A, C-I). e_ijk_ is the random error term of the model that is assumed to be normally distributed with homogeneous variance.

Assumptions made:

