**Table 6 Tab6:** **Power calculations for some selected variables**

Outcome measure all on the monthly scale	Effective sample size?	Assumed normal distribution	Shift amount (K)	SPower
PBS Total cost	30	Log(PBS Total cost+1)	1	1.00
MBS out of hospital costs	30	Log(MBS out of hospital costs+1)	1	1.00
MBS in hospital costs	30	Log(MBS in hospital costs+1)	1	0.84
Number of hospital admissions	30	Square root the number of hospital admissions	0.5	0.99
Number of GP visits during working hours	30	Square root of number of GP visits during working hours	0.5	0.89
Number of GP visits outside of working hours	30	Square root of number of GP visits outside of working hours	0.1	0.50
Total number of GP visits	30	Square root of total number of GP visits	1	0.97
Total number of either Specialist, Psychiatric, Allied Health visits and Procedures	30	Square root of total number of either Specialist, Psychiatric, Allied Health visits and Procedures	1	0.77
Total number of Laboratory tests	30	Square root of total number of Laboratory tests	1	0.97
Number of Laboratory	30	Square root of number of Laboratory	1	0.96
Tests		Tests		

The actual results may be much more complicated than this because the differences between the outcome variables may be auto correlated. This is particularly true if the test patient and the matched control patient outcome measures have different time series trends. Testing of whether the matched differences are auto correlated will be carried out when data becomes available but is not expected to be a significant problem.

The actual results may be much more complicated than this because the differences between the outcome variables may be auto correlated. This is particularly true if the test patient and the matched control patient outcome measures have different time series trends. Testing of whether the matched differences are auto correlated will be carried out when data becomes available but is not expected to be a significant problem.

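### The article names two different deciding tests and no lead outcome, and it applies one unadjusted 0.05 rule to at least ten overlapping outcomes

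*Protocol article*

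**What the plan says.** **Deciding test.** Data analysis holds that only Test-Control matched pairs can be compared validly, by paired or repeated-measures t-tests. It adds that "all tests of whether the intervention made a difference will involve a one-tailed matched pair t-test". The criterion is that "a p value of 0.05 or less will be used to indicate statistical significance". The same sentence allows an alternative to the p value: "or a confidence interval will be provided to judge the impact of the intervention".

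Classical BACI designs and extensions takes another course. It begins "Since standard BACI design cannot be used when study variables trend over time", adopts a linear mixed model, and states that this model "tests whether a significant change has occurred by testing the significance of the interaction term" between the before-after and control-intervention indicators. The abstract reports from preliminary data that most outcomes are not stationary, so the condition for leaving the standard design is met. The text on Figure 5 describes the expected impact as a change of slope in Test patients.

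**Outcomes.** None is called primary. The mixed model is offered for any variable analysed, and Table 6 powers ten rows on equal terms.

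**Hospital outcome.** The research questions speak of unscheduled hospital visits. A project objective is to show the potential to "reduce unscheduled admissions to Accident and Emergency (A&E) compared to the control group", and a separate objective covers hospital admissions. Table 5 lists "Number of unscheduled admissions to hospital for their condition". Table 6 powers "Number of hospital admissions" without restriction. The note under Table 1 defines unplanned admissions for the study, with no restriction by condition.

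**The concern.** An analyst following Data analysis to the letter would run a test that the next section treats as unsuitable for most of the outcomes. An analyst following the next section would breach the statement that all intervention tests are paired t-tests. The two differ in how they handle trend, in the parameter tested and, as far as the text goes, in sidedness: one-sided for the t-test, unstated for the interaction. If they disagree, nothing says which prevails.

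With no lead outcome, every Table 6 row can be called significant at one-sided 0.05. The trial is meant to inform government funding policy, so a reader needs to know beforehand which result counts.

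**Working it through.** **1. Which parameter is tested.** The model equation is not legible in the text, so this uses its list of terms. Write B and A for before and after, C and I for control and intervention. In the Test-Control, after-minus-before contrast the mean, the period and group main effects and the common slope cancel. At month k this leaves

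D(k) = L + k × S

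- L = [(αβ)_AI − (αβ)_BI] − [(αβ)_AC − (αβ)_BC], the level interaction that the article tests
- S = [θ_AI − θ_BI] − [θ_AC − θ_BC], the change of slope that the Figure 5 text expects

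Assume a pure slope change with no jump when the intervention starts, at month k0. Then D(k0) = 0, so L = −k0 × S.

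- Time counted from the start of the intervention: k0 = 0 and L = 0. The named test has nothing to detect.
- Time counted from the start of the data: the series is 4.5 years (54 months) including 6 to 18 months of intervention, so k0 = 54 − 18 = 36 to 54 − 6 = 48. Then L = −36S to −48S, opposite in sign to the benefit.

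The article does not state the time origin. In neither case does L alone measure the expected effect.

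**2. False-positive chance over outcomes.** Inputs: threshold 0.05 one-sided (Data analysis); ten outcomes (Table 6); no true effect on any.

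- Independent: 1 − 0.95^10 = 0.401. If the two laboratory rows are one outcome: 1 − 0.95^9 = 0.370.
- Equally correlated normal test statistics, 400,000 simulated draws, ten outcomes:

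| Assumed correlation | P(at least one p ≤ 0.05) |
|---|---|
| 0.3 | 0.31 |
| 0.5 | 0.25 |
| 0.7 | 0.19 |
| 0.9 | 0.12 |

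The article gives no correlations. Rows clearly overlap (total GP visits contains the in-hours and out-of-hours rows), so independence is not realistic.

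**3. Two tests on one outcome.** If a significant result on either test counts, 0.05 becomes 0.068 at a between-test correlation of 0.9 and 0.097 at zero (simulated; correlations assumed).

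**4. Table 6.** Its powers cannot be reproduced: σ and ρ have no values in the text and the formula is not legible. They are for a matched-pair t-test with effective sample size 30. For the mixed model, Power calculations says only that power is hard to compute. Back-solving the standardised effect d from the stated power (noncentral t, n = 30, one-sided 0.05) gives:

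- hospital admissions: power 0.99, d = 0.743, SD of differences 0.5/0.743 = 0.67 on the square-root scale
- MBS in-hospital costs: power 0.84, d = 0.494, SD = 1/0.494 = 2.03 (from the unrounded d) on the log scale

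Holding d fixed and testing at 0.05/10 = 0.005, power falls from 0.99 to 0.90 for admissions, from 0.84 to 0.49 for MBS in-hospital costs, and from 0.89 to 0.58 for in-hours GP visits. This shows the price of adjustment; it does not verify the table.

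**The case against.** Several points on the other side are fair.

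- **The tests are not simply rivals.** Data analysis announces both conventional and model-based methods, the abstract ties the mixed model to non-stationarity, and the BACI section notes that Test-Control differences simplify the analysis. One can infer that the mixed model leads for trending outcomes. That stands as an inference. The statement that all intervention tests are paired t-tests still contradicts it, and taking differences settles neither the trend terms nor the sidedness.
- **A reader might infer that the powered outcome is in no objective.** The document does not support this: hospital admissions are an objective of their own, beside the A&E one. What remains is that the powered variable is not limited to unscheduled admissions, and that Table 5 has no A&E variable for the A&E objective.
- **A reader might infer four competing definitions of the hospital outcome.** There are four names and one definition, the study-wide one under Table 1. Some names may denote distinct outcomes.
- **A reader might take 40% as the error rate, or one significant row in ten as declared success.** The overlap of rows makes 40% an upper bound, and the article states no such success rule. It also permits judgement by confidence interval.
- **A multiplicity procedure may sit in an analysis plan that is not shown.** Agreed: its absence alone is no fault. The fault is what the article does state: a single threshold for every intervention test, and two conflicting deciding tests.

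**Conclusion.** The point holds in this form. The conflict between Data analysis and the BACI section is in the text and needs no assumption. So is the mismatch between the level interaction that is tested and the slope change that is expected; its numerical illustration assumes no jump at the start of the intervention. With ten outcomes and no true effect, the chance of at least one significant benefit is about 12% to 31% for assumed equal correlations of 0.9 to 0.3. It exceeds 5% across that whole range. The inconsistent naming of the hospital outcome is a lesser but real defect, because it leaves open which result answers the main question.

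**What to change.** 1. Amend Data analysis so that the mixed-model before-after Test-Control contrast, stated to include the slope terms, is the single deciding analysis. Make paired t-tests supportive, and state sidedness once for the whole plan.
2. Name one lead outcome: unplanned hospital admissions as defined under Table 1. The sponsor should state whether this means all causes or the patient's own condition. Use the same wording in the research questions, the objectives, Table 5 and Table 6.
3. Report the other outcomes either with Holm adjustment or as estimates with confidence intervals and no claim of significance.
4. State that the Table 6 powers apply to the paired t-test only.

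No recruitment or data collection changes. With one lead outcome and one test, 0.05 needs no correction. The cost is that secondary claims become harder to make, and that the deciding test would be one whose power the article does not give.
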